#### Telephone counsellor background and training

All telephone counsellors have at least bachelor's level training in nutrition and dietetics; some have also completed a dual-degree in exercise physiology. They undergo one month of intensive training in study protocols and a motivational interviewing approach to health behaviour counselling [70] (including role plays with study investigators). Telephone counsellors have ongoing quality assurance checks via randomly taped telephone calls and fortnightly clinical supervision meetings. In addition, call attempts, completions and duration are tracked, and a call content checklist completed after each call to inform an evaluation of intervention fidelity. To the extent possible, the same telephone counsellor remains with participants throughout the duration of the intervention to facilitate rapport and continuity of care.

#### Intervention procedures

Intervention delivery is guided by a patient-centred, chronic disease self-management intervention model used in previous trials (Figure 1) [37,71], and by techniques of motivational interviewing [70]. An iterative process is used in each call: it draws upon repeated *assessment *of study outcomes and participant self-monitoring; *feedback *is provided in relation to study targets for weight, dietary intake and physical activity, and consistent with a motivational interviewing approach, this feedback highlights the discrepancy between participant goals and their current health behaviours; *collaborative goals *for weight, physical activity and dietary change are set with the telephone counsellor, with an emphasis on achievability and measurability. Each intervention contact results in a *behaviourally-specific Action Plan *that specifies exactly what is to be done and when; *barriers and supports *are identified; *confidence *is assessed and *problem-solving *is discussed as necessary. These steps are repeated during intervention calls, with goals being adjusted as necessary.

**Figure 1 F1:**
[figure not shown]
**Chronic Disease Self-Management Intervention Model**.

A semi-structured approach to both the content and the order in which intervention targets are addressed is used to guide intervention delivery (see Table 2). However, consistent with the motivational interviewing approach, the intervention is tailored to each participant, with an initial focus on targets in which she/he is most motivated and most confident in changing.

**Table 2 T2:** Telephone Intervention Overview: Call Frequency and Content

Intervention stage & call frequency	Purpose	Content
**Phase 1**: Month 1 4 weekly calls	Building rapport	Program introduction/explanation Participant overarching program goals Feedback on baseline assessment Review & goal-setting: *Weight loss*: benefits, energy balance, realistic targets, portion sizes, recommended serves, reducing fat intake Behaviour change skills: self-monitoring, goal-setting Begin use of scale, pedometer and food diary

**Phase 2**: (Months 2-6) 11 fortnightly calls	Behaviour change Weight loss Skill-building	Review & goal-setting: *Physical activity*: planned activity, incidental activity, sitting time, strength training *Diet*: reducing energy intake (choosing lower energy foods, swapping higher energy foods for lower energy foods, decreasing intake of high energy foods/drinks), eating habits, food labels, modifying recipes Behaviour change skills: rewards, behavioural cues, barriers and supports Progress review at 3 months

**Phase 3**: (Months 7-18) 12 monthly calls	Maintenance of behaviour change & weight loss	Feedback on 6-, 12- & 18-month assessments Progress review at 9 & 15 months Review & goal-setting: Role of physical activity in maintaining weight loss Problem-solving Social-environmental support Developing lifelong habits

##### Phase 1 (month 1)

The first month of the intervention involves up to four weekly calls, with a focus on building rapport (e.g. providing feedback on the baseline assessment and understanding what the participant wants to get out of the program); education on weight loss (e.g. energy balance); and skill-building (e.g. self-monitoring and goal-setting). The emphasis is on helping participants to gain the knowledge and skills necessary to achieve behaviour change and weight loss in the next phase.

##### Phase 2 (months 2-6)

Up to 11 fortnightly calls are completed during this phase, with an emphasis on initial behaviour change, weight loss and continued confidence and skill-building. Behaviourally-specific goal setting with regard to the amount of physical activity and dietary change that is needed to achieve weight loss is the focus, along with problem-solving and continued self-monitoring.

##### Phase 3: (months 7-18)

This phase of the intervention involves 12 calls over 12 months (one per month) with a focus on maintenance of behaviour change and weight loss. During this phase, participants not yet reaching their initial weight loss, physical activity and/or dietary behaviour change targets are encouraged to continue to work towards these; those who have reached initial targets focus on strategies for maintaining weight loss and behaviour change. In addition to continued support from telephone counsellors, other strategies to promote maintenance include: ongoing self-monitoring, enlisting social support (from family, friends and health care providers), and use of community resources to support lifestyle change (e.g., weight loss groups, walking tracks, gym membership).

### Primary and secondary outcomes

Primary outcomes are: change in weight (kg), accelerometer-measured moderate-to-vigorous physical activity and glycaemic control (HbA1c). Secondary outcomes are: change in self-reported dietary and energy intake, accelerometer-measured light intensity and sedentary time, objectively measured waist circumference, percent body fat, fasting plasma glucose and blood lipids (total cholesterol, HDL-cholesterol, LDL-cholesterol, triglycerides), liver function enzymes, blood pressure, along with self-reported SCE constructs, medication use and health-related quality of life. We will also evaluate the incremental cost-effectiveness of the telephone intervention and examine demographic and health-related moderators of intervention effects and mediators consistent with the underlying theoretical basis. Related measures are described below and summarised in Table 3.

**Table 3 T3:** Summary of Measures

**Anthropometric**	**#**Weight****
	#Waist circumference
	% body fat
	
Cardio-metabolic	**Glycoslyated haemoglobin**
	Fasting blood glucose
	Cholesterol (total, HDL, LDL)
	Triglycerides
	Liver function tests (ALT, AST, LDH, ALP, GGT)
	Blood pressure
	Diabetes medication
	
Behavioural	#**Objectively measured physical activity (PA) via accelerometer**
	Average mod-vig PA/day (mins)
	Average light intensity PA/day (mins)
	Average very light intensity PA/day (mins)
	Average sedentary time/day (mins)
	Breaks in sedentary time (n/day)
	Bouts of moderate-to-vigorous intensity activity (n/day)
	Self-reported physical activity
	Walking (days & min/wk)
	Walking for exercise (days & min/wk)
	Moderate-vigorous PA (days & min/wk)
	Resistance training (days & min/wk)
	Sitting items (transport, television, computer min/wk)
	Self-reported diet
	Dietary intake (total energy, total fat, saturated fat, fibre)
	Dietary behaviour
	Sleep (duration & quality)
	
Psychosocial-Environmental	Depression
	Self-efficacy
	Social support
	Perceptions of the neighbourhood environment
	
Cost-effectiveness	Health-related quality of life
	Health care utilization
	Cost to deliver intervention
	
Intervention Delivery (tracked for each call)	Call duration
	Call completion

All assessed at baseline, 6, 18 & 24 months; #assessed at 12 months; bold text denotes primary outcome

### Data collection

Data are collected via objective measurements conducted in participants' homes, telephone interviews, and self-administered questionnaires at baseline, 6-, 18-, and 24-months by research staff and registered nurses blind to participants' study group. At 12 months, weight, waist circumference and accelerometer-derived physical activity are also assessed. Home visits are conducted by registered nurses and include objective measurement of: height (baseline only; Seca 214 height rod, Seca, Germany), weight, waist circumference, body composition, blood pressure and collection of blood samples for biochemical assay. In addition, details of diabetes medications (drug and dosage) and any use (yes/no) of antihypertensive and lipid-lowering medications are also collected during this visit. Telephone interviews collect self-report data on: demographics (gender, age, education, income, type and number of chronic conditions; baseline only), and validated measures of physical activity, diet, quality of life and health care use, as well as items to assess sleep, diabetes history and management, use of weight loss aids and adverse outcomes. Self-administered questionnaires are used to collect data related to the social-cognitive and environmental constructs which underpin the intervention and to assess depression. In addition to the self-reported physical activity collected via the telephone interviews, accelerometers are used to collect objectively-measured physical activity and sedentary time. Data related to intervention delivery are also tracked by telephone counsellors following each call. This includes data on call outcomes (call completion versus missed calls), call duration and call content (via a checklist of topics). Details of the measures are provided below and summarised in Table 3.

#### Anthropometric outcomes

##### Weight loss

Weight is measured without shoes or heavy clothing to the nearest 0.1 kg using standard calibrated scales (Model TI TBF 350, Tanita Inc., Tokyo, Japan).

##### Waist circumference

Waist circumference is measured with a non-expandable tape to the nearest 0.5 cm at the superior border of the iliac crest [12,72]. Waist measurements are taken in duplicate and a third measurement taken if the first two differ by more than 1 cm. The mean of the measurements is used.

##### Body composition

Fat mass (kg), fat free mass (kg) and percent body fat are measured using foot-to-foot bioelectrical impedance analysis (Model TI TBF 350, Tanita Inc., Tokyo, Japan) in the fasted state. Body composition measurements are not performed on participants with a pacemaker.

#### Cardio-metabolic outcomes

Blood samples are taken early in the morning after an overnight fast (at least 10 hours), with participants instructed not to take any glucose-lowering medication prior to the assessment.

##### Glycaemic control

HbA1c is measured from whole blood samples by the high performance liquid chromatography method (Bio-Rad Variant II, Sydney, Australia). Plasma glucose is measured by the hexokinase method (Roche Modular Analyzer; Tokyo, Japan).

##### Blood lipids

Total cholesterol, high density lipoprotein (HDL) cholesterol and triglycerides are measured by an enzymatic colorimetric assay with Roche Modular Chemistry Analyser (Tokyo, Japan). Low density lipoprotein (LDL) cholesterol is determined using the Friedewald equation [73,74].

##### Liver function tests

Liver enzymes - alanine amino-transferase (ALT), aspartate amino-transferase (AST), lactate dehydrogenase (LDH), alkaline phosphatase (ALP), gamma glutamyl transpeptidase (GGT) - are measured using Roche Modular (Tokyo, Japan).

##### Blood pressure

Blood pressure is measured in the seated position by a portable sphygmomanometer (Gamma G5, Heine, Germany) using the non-dominant arm and an appropriately sized cuff. Two readings are taken and a third measurement taken if the first two differ by more than 10 mmHg systolic or 6 mmHg diastolic, or if the first two readings are more than 140/90 mmHg. Blood pressure is recorded as the mean of the readings taken.

##### Medication use

Details of diabetes medication (oral medication and insulin) are collected by registered nurses from prescription containers - medication name, dose prescribed and daily quantity taken. Participants are also asked to report whether they are taking anti-hypertensive or lipid-lowering medications.

#### Behavioural outcomes

##### Objectively-measured physical activity and sedentary time

A dual-axis accelerometer (Actigraph model GT1M; Actigraph, LLC, Fort Walton Beach, Florida), fitted firmly around the waist by elasticised band and positioned on the right mid axillary line, is used to objectively-derive physical activity and sedentary time. Participants are instructed to wear the accelerometer during all waking hours (removing for any water based activities) for a continuous period of seven days, and to record time worn in a wear-time log. The study nurse demonstrates how to wear the accelerometer and complete the wear-time log. Research staff then telephone the participant to negotiate a start date and reiterate the instructions; the accelerometer and wear-time log are then posted to participants. On the (expected) seventh day of wear, a follow-up telephone call is made by research staff to ensure adequate wear time and to prompt accelerometer return in a reply-paid envelope. The protocol for the follow-up assessment is identical with the exception that the registered nurse does not repeat the demonstration and instructions at the assessment.

Accelerometer data are collected in one minute epochs. A generic program (SAS 9.1), modified from the National Cancer Institute [75], is used to identify outliers and summarise daily variables. The wear time syntax of the program, based on a combination of the wear-time logs and the accelerometer data, is modified for each participant in order to maximise the accuracy of the wear time estimation. Invalid days of observation (days with < 10 hours wear or excessive counts ≥ 20,000 counts per minute: cpm) will be discarded. Daily sedentary (< 100 cpm), very light-intensity activity (100 to 759 cpm), light-intensity activity (760 to 1951 cpm), moderate-intensity activity (1952 to 5724 cpm), and vigorous-intensity activity (≥ 5 725 cpm) [76,77] time are calculated and standardised for wear time using the residuals method [78]. Patterns of physical activity and sedentary time accumulation (for example, breaks in sedentary time [79] and bouts of moderate-to-vigorous intensity activity) [80] are examined. Data are reported as averages for valid days. The data collection and analytic protocol comply with the best-practice guidelines for conducting accelerometer-based activity assessments in field-based research [81].

##### Self-reported physical activity

Self-reported physical activity is measured by the Active Australia Survey (AAS), a 6-item measure assessing frequency and total duration per week spent on walking, vigorous and moderate physical activities over the last seven days [47]. The frequency items have been adapted to ask about number of 'days per week' instead of 'sessions per week'. Total minutes of physical activity is calculated from the sum of walking, moderate and 2 × vigorous minutes and truncated at 1,680 minutes per week [47]. Two items from the U.S. National Health Interview Survey (NHIS) have been adapted to assess the number of days and amount of time in the past week spent walking for exercise [82]. The AAS has been found to have acceptable validity and reliability [83], the NHIS items have shown acceptable validity [82] and both items have shown similar or greater responsiveness to change compared to a more detailed self-report instrument [84].

##### Self-reported resistance training

Using a response format similar to that of the AAS, the number of days and total number of minutes per week of resistance training are collected using an unvalidated item [85].

##### Self-reported sitting time

Six items are used to assess total time spent sitting in the last week across three domains - 1) transport, 2) watching television, videos or playing electronic games and 3) leisure-time computer use - asked separately for weekdays and weekend days. These items have shown good test-retest reliability (unpublished data).

##### Dietary intake

Diet is assessed using the Anti-Cancer Council of Victoria (ACCV) Food Frequency Questionnaire (FFQ) (version 2). The FFQ includes 74 food items and six alcoholic beverage items with responses on a 10-point scale (1 = Never to 10 = 3 or more times per day), four pictorial questions relating to portion size, one question on quantity of alcoholic beverages and 10 cross-check questions used to adjust for overestimation and types of food products consumed (milk, bread, spread and cheese) [86]. It was modified to ask about intake over the previous month instead of the previous 12 months and to be telephone administered instead of self-administered (participants receive a copy of the portion size pictures in the mail). Nutrient intakes are computed from FFQ responses using software developed by the ACCV based on the NUTTAB95 nutrient composition data [87]. The questionnaire estimates intakes of most nutrients accurately (within 10%) and does not systematically under- or over-estimate against weighed records [86].

In addition to the FFQ, dietary behaviours and intakes of specific food groups will also be assessed. Servings of vegetables and fruit are assessed using items from the Australian National Nutrition Survey which have demonstrated validity against more comprehensive self-reported measures [88] and biomarkers (serum carotenoids and red-cell folate) [89]. The 20-item Fat & Fibre Behaviour Questionniare is also administered. This questionnaire was used in our previous trial [40] and adapted from other short dietary questionnaires [90-93] to assess behaviours related to fat and fibre intake that were targeted as part of the intervention. This index has shown good two-week test-retest reliability (ICC = 0.87-0.89), Pearson's correlations of 0.50-0.56 for relative validity compared to FFQ and similar or higher responsiveness compared to FFQ (unpublished data).

##### Sleep

A single item to assess sleep duration on weekdays or workdays in the past week (reported in hours and minutes) was adapted from an existing instrument with established reliability and validity [94-96]. A single item to assess sleep quality (in terms of feeling rested upon awakening; rated from 1 = excellent to 5 = poor) was created.

#### Psychosocial-environmental outcomes

##### Depression

Measured using 9-items from the PRIME-MD Patient Health Questionnaire (PHQ) assessing depressive symptoms over the last two weeks, with items answered on a 4-point scale (0 = not at all; 1 = several days; 2 = more than half the days; 3 = nearly every day). Items are summed such that higher scores indicate a higher depression symptom severity, which has shown good criterion validity compared to a Mental Health Professional interview (*r *= 0.84) [97].

##### Eating and exercise self-efficacy

Measured using a 10-item questionnaire that assesses confidence in ability to follow exercise and eating plans in difficult situations (e.g., confidence in exercising when sore or tired; confidence to choose healthy food options when bored) [98]. Items are answered on a scale from 0 (not at all confident) to 8 (extremely confident), and summed to create a 5-item eating self-efficacy scale and 5-item exercise self-efficacy scale, which have shown good internal consistency - Cronbach's *α *= 0.87 and 0.91, respectively [98].

##### Confidence in weight loss

Using the format and scale above, a single item on confidence in losing weight through exercise and healthy eating was adapted for this study from the Multidimensional Diabetes Questionnaire [99].

##### Social support for diet and physical activity

Measured using a 20-item questionnaire assessing the frequency of family and friend support over the previous three months for healthy eating and exercise (e.g. complimented you on your progress in making healthy changes to your diet; exercised with you); answered on a 5-point scale (1 = none of the time; 5 = very often) [100]; and summed separately for diet and physical activity. The questionnaire was adapted to ask about support received from 'friends, family or members of your household' combined, instead of asking questions separately for support from 'friends' and from 'family.'

##### Perceptions of the neighbourhood environment

Measured using 10-items created to assess neighbourhood attributes related to walking for exercise or transport (i.e., aesthetics, convenience, access and traffic); answered on an 11-point scale (-5 = strongly disagree; +5 = strongly agree, with 0 = neutral option). The items were selected or modified from existing instruments [101,102].

#### Cost-effectiveness

##### Health-related quality of life

The Short-Form (SF)-12 Version 2 Health Survey [103], validated for use in Australia [104,105], is used to assess health-related quality of life across eight dimensions - physical functioning, social functioning, role limitations due to physical problems, role limitations due to emotional problems, bodily pain, vitality, general health and mental health. To enable economic analysis, the SF-12 is converted to EQ-5 D preference based utility values via an algorithm developed by Gray and colleagues [106].

##### Health care utilisation

Measured using 9-items assessing doctor and allied health care visits and hospital stays in the past six months [107]. Dollar valuations of these resources are obtained from the Commonwealth Government schedule of re-imbursements [108] and are used in cost-effectiveness analysis.

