#### Incremental cost-effectiveness

A probabilistic decision analytic Markov model developed for our recent telephone-delivered lifestyle intervention trial will be adapted and used to evaluate incremental cost-effectiveness [42]. The structure, data requirements, methods for calibration and model evaluation are described in a recent methodological peer reviewed publication [91]. The model describes the health states relevant to intervening on weight loss, physical activity, and glycaemic control in adults with type 2 diabetes. A societal perspective is adopted and values collected for variables that describe the participant's use of acute and primary care health services, their private out of pocket expenditures and the time costs to informal carers. Patient-based production losses are not included on the cost side of the analysis but (implicitly) counted within the QALY estimation in line with current theory and recommendations [92]. The model implies the trial participants face some probability of remaining in a sub-optimal health state or transitioning to improved health states (i.e. improvements in weight, physical activity and glycaemic control) and there will be a small chance of transitioning to death. Cycle duration is based on the timing of data collection for health-related quality of life (i.e. baseline, 6, 18, and 24 months). The transition probabilities that reflect consistency with study intervention targets surrounding primary outcomes (i.e., 5% weight loss, 210 min/wk moderate-to-vigorous PA, < 7% HbA1c) will be used to predict movement through the states for all cycles; this approach is shown in a previous economic analysis [42]. Costs and utility based preference scores will be estimated for each cycle and summarised to estimate change in costs and change in QALYs. The relevant ICER will be estimated and cost-effectiveness acceptability curves plotted to illustrate the probability that the intervention is cost-effective [109].

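### The health-care use items recall six months and are not asked at month 12, so months 6–12 are unmeasured and the health-care-use part of the 6–18 month model cycle is observed for only half its length

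*Protocol article*

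**What the plan says.** The section Health care utilisation describes the instrument as "9-items assessing doctor and allied health care visits and hospital stays in the past six months". It adds that the resources are given dollar values that "are used in cost-effectiveness analysis".

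The section Data collection puts these items in the telephone interview, which gathers "validated measures of physical activity, diet, quality of life and health care use". It gives the timing as "telephone interviews, and self-administered questionnaires at baseline, 6-, 18-, and 24-months by research staff and registered nurses". The 12-month assessment is described separately and is short: "At 12 months, weight, waist circumference and accelerometer-derived physical activity are also assessed".

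The footnote to Table 3 agrees: "All assessed at baseline, 6, 18 & 24 months; #assessed at 12 months". Health care utilization has no # mark in that table.

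The section Incremental cost-effectiveness sets the model's time steps: "Cycle duration is based on the timing of data collection for health-related quality of life (i.e. baseline, 6, 18, and 24 months". It then states that "Costs and utility based preference scores will be estimated for each cycle and summarised to estimate change in costs and change in QALYs".

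**The concern.** The recall period, the interview schedule and the cycle lengths are all stated, and they do not fit together. A six-month recall works when interviews are six months apart. Between months 6 and 18 they are twelve months apart, and the model treats that interval as one cycle needing one cost.

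The mismatch matters for resource use in particular. A quality-of-life utility is a value at a point in time and can be interpolated between months 6 and 18. A count of visits and stays over a fixed window says nothing direct about the months outside it.

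At stake is the health-care-use part of the incremental cost, and through it the ICER. The article presents cost-effectiveness as one of the study's contributions. None of the three primary outcomes is affected.

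**Working it through.** **Inputs**
- Recall length: 6 months (Health care utilisation).
- Interviews containing the items: months 0, 6, 18 and 24 (Data collection; Table 3 footnote).
- Model cycles: 0–6, 6–18 and 18–24 months (Incremental cost-effectiveness).

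The article gives no coverage figure to reproduce.

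**Coverage.** An interview at month t covers t − 6 to t.
- Month 0: the six months before enrolment.
- Month 6: months 0–6.
- Month 18: months 12–18.
- Month 24: months 18–24.

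| Interval | Months observed | Share | Not observed |
|---|---|---|---|
| Cycle 0–6 | 6 of 6 | 100% | none |
| Cycle 6–18 | 6 of 12 | 50% | 6–12 |
| Cycle 18–24 | 6 of 6 | 100% | none |
| Whole follow-up | 18 of 24 | 75% | 6–12 |

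**Effect on cost.** Write U(a–b) for health-care cost between months a and b in one arm. The article does not say how the 6–18 cycle is to be filled, so two ways are shown.

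1. *Six-month total entered unscaled.* The cost recorded over 24 months is the true cost minus U(6–12). With a constant monthly cost c, the truth is 24c and the record is 18c. The shortfall is 6c / 24c = 25% over the trial and 6c / 12c = 50% within the middle cycle. A constant between-arm difference in health-care cost shrinks by the same 25%.

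2. *Months 12–18 doubled to fill the cycle.* The error in each arm is 2 × U(12–18) − [U(6–12) + U(12–18)] = U(12–18) − U(6–12). It is zero if use is constant. An arm's cost is right only if its months 6–12 matched its months 12–18. The error in the incremental cost is the intervention-arm error minus the usual-care-arm error, so it vanishes if the shift between the two half-years is the same in both arms. With no data for months 6–12, neither condition can be checked.

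**After the fix.** With the same items also asked at month 12, that interview covers months 6–12. Coverage becomes 12 of 12 months in the middle cycle and 24 of 24 overall.

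**The case against.** Five points can be made on the other side.

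- *Some events in the gap may be recorded elsewhere.* The Adverse outcomes monitoring system asks at each follow-up telephone interview about health problems arising since the last contact, and gives hospital stays as an example. The 18-month interview may therefore pick up some admissions from months 6–12. This stands in part. The question yields free-text event reports, does not count routine doctor or allied health visits, and is not the instrument named for costing. The last contact might also be read as the 12-month one.

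- *The whole cycle cost is not half missing.* This stands. The section Intervention costs says delivery costs are tracked during implementation, so only the health-care-use component has the gap.

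- *A reader might infer that the plan understates cost by 25%.* The article does not support that. It says costs are estimated for each cycle, not that raw six-month totals are entered. Under the constant use that the 25% assumes, simple scaling removes the error entirely.

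- *A reader might also infer that months 6–12 are when the arms are most likely to differ.* The article does not support that either. The intensive phase is months 1–6, which the 6-month interview covers in full. Months 7–18 form one maintenance phase with monthly calls, so the unobserved half-year lies in the same phase as the observed months 12–18. That makes extrapolation more defensible. A difference remains possible, because only the intervention arm receives calls, and those participants are referred to their GP when new health concerns arise.

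- *The full protocol or the cited modelling paper may contain an extrapolation rule.* It may. Such a rule would decide how the gap is filled, but it would not supply data that were never collected.

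**Conclusion.** The point holds for the health-care-use component of cost. On the stated schedule the nine items leave months 6–12 unmeasured: 6 of the 12 months in the 6–18 month cycle, and 6 of 24 months overall.

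Under constant use, the understatement of 24-month health-care cost lies between 0 (months 12–18 scaled up) and 25% (totals entered unscaled, the worst case). If use is not constant, the error depends on use in months 6–12, which the documents give no means of estimating. Its direction in the incremental cost is unknown. This is a weakness in the economic evaluation that is cheap to repair, and it does not threaten the primary outcomes.

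**What to change.** Add the nine items, with their six-month recall unchanged, to the 12-month contact. That contact already exists. The accelerometer procedure involves staff telephoning participants, and the article says follow-up assessments repeat it apart from the nurse's demonstration. The cost is a few minutes of telephone time per participant.

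For participants already past month 12:
- cost months 6–12 explicitly from the adjacent windows, for example as the average of use in months 0–6 and 12–18;
- do not enter six months of cost for the 12-month cycle;
- vary the months 6–12 value in the probabilistic sensitivity analysis, allowing it to differ between arms.

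Asking about the past 12 months at the 18-month interview would also close the gap, but it is a less preferred fallback. It departs from the six-month recall used at the other waves and asks participants to remember further back.
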